### Eligibility Criteria

To work with a homogenous study population and to reduce the influence of different characteristics of the study population on study outcomes, the inclusion and exclusion criteria for participating in the study were chosen as listed in Textbox 2. It is known that both neural and behavioral processing of stress is altered in clinical samples with conditions such as depression [55] or anxiety disorders [56]. To minimize differences between participants, we excluded individuals with current or past psychological treatment as assessed in our standardized telephone screening. To reduce the impact of hormonal contraceptives in women on stress reactivity (saliva cortisol) and emotional memory [57], only women taking no hormonal contraceptives are included in our study. Alcohol abuse was defined according to the *Diagnostic and Statistical Manual of Mental Disorders* (Fourth Edition) [58] as a regular or daily drinking routine.

Inclusion and exclusion criteria.
**Inclusion criteria**
Age: 18-45 yearsNonsmokersNormal blood pressure (≤140/90 mm Hg)Suitable for sportsVoluntary participationNo medicationPhysically inactive (<150 minutes/week physically active)Time for 8-week interventionSigning the consent formGender: male and female
**Exclusion criteria**
Age: <18 or >45 yearsSmoker or other tobacco consumptionHigh blood pressureNot suitable for sportsConstrained participationLong-term medication intakeTrained (>150 minutes/week physically active)Probably no time for interventionRejection by the participantLack of ability to consent or doubts about the ability to consentHairless participants (<1 cm)Shift workerClinically significant 12-channel electrocardiogram abnormality determined by the physicianAlcohol or drug abuse within the past year before screening, positive urine drug test, or positive alcohol test during screeningInfection with HIV, Hepatitis C virus, or Hepatitis B virusParticipation in another studyOther unspecified reasons that, from the investigator's point of view, militate against participation in the studyCardiovascular, metabolic, pulmonary, and muscular diseases after the *International Classification of Diseases, Tenth Revision*, acute or anamnesticPsychological disorders diagnosed according to *International Classification of Diseases, Tenth Revision* or *Diagnostic and Statistical Manual of Mental Disorders* (Fourth Edition), acute or anamnestic (last 24 months)Female participants taking hormonal contraceptives

### Preliminary Investigation (T0/T1 and T2/T3)

The first visit (T0) includes the initial screening of the participant’s height and weight. A pulmonary function test will be used to determine vital capacity, forced expiratory volume in 1 second (Spirometry, Bodybox 5500, Medisoft Group) and, if applicable, to identify the presence of undiagnosed restrictive or obstructive respiratory abnormalities [59]. Furthermore, the cardiological values of resting blood pressure and resting electrocardiogram (Schiller AT-60) will be measured in a supine position to ensure proper cardiovascular function. To determine the long-term cortisol value over 2 months, a 2 cm–long strand of hair will be cut off at the back of the head directly from the skin [60]. A bioelectric impedance analysis (In Body 3.0, Biospace) and blood counts will be conducted during the second visit (T1) in the morning before the incremental running test after a minimum of 8 hours of overnight fasting. After the completion of the control or exercise intervention, the described parameters will be reassessed during the third or fourth visit (T2 or T3).

### Questionnaires (T0 and T2)

Owing to the multidimensional approach to stress resilience outlined above, we required a lot of information about the participants’ lifestyle as well as psychological and medical anamnesis with the help of several questionnaires. To minimize the total experimental time, participants will complete part of the questionnaires on the web before their arrival at T0. Further questionnaires will be completed within the resting and recovery periods during the on-site appointments.

#### Psychological Questionnaires

##### Brief Resilience Scale (Only T0)

The Brief Resilience Scale is a 6-item questionnaire that considers the dimension *bounce back* from stress on a 5-point Likert scale. The scale exhibits good psychometric properties with high internal consistency and retest reliability [61]. The German version of the Brief Resilience Scale was validated in 2018 [62].

##### Childhood Trauma Screener (Only T0)

The Childhood Trauma Screener (CTS) is a 5-item brief instrument for the assessment of childhood abuse and neglect on a 5-point Likert scale [63]. The CTS is based on the Childhood Trauma Questionnaire, which includes 28 items on physical, emotional, and sexual abuse as well as emotional and physical neglect [64,65]. These questions of the CTS deal with experiences during childhood and youth. The CTS showed a high correlation (*r*=.88; *P*<.001) with the total Childhood Trauma Questionnaire score. The internal consistency was .757 (Cronbach α; n=499).

##### Brief Symptom Index-18

The Brief Symptom Index-18 is an 18-item scale, which is divided into 3 syndromes—somatization, depression, and anxiety—with 6 items each on a 5-point Likert scale [66]. The German version of the Brief Symptom Index-18 was validated in 2011. It showed a satisfactory-to-high consistency of the different syndromes (Cronbach α between .63 and .93) [67].

##### General Depression Scale (Long Version)

The General Depression Scale (German translation: *Allgemeine Depressionsskala* [ADS]) is the most common German version of the Center for Epidemiologic Studies Depression Scale [68]. The first test publication of ADS was in 1993 [69]. The second edition of the manual with new samples and standard data was published in 2012 [70]. No changes were made to the items. Only the critical threshold value of the long version (ADS-L) for the screening of depression was corrected from >23 to >22 [70]. With its 20 items, the ADS-L considers affective, cognitive, somatic, and social depression symptoms, among others. The answers are given on a 4-point scale from 0 (rarely or not at all [<1 day]) to 3 (mostly all the time [5-7 days]). The internal consistency (Cronbach α) of the ADS-L in adults in multiple population samples is between .85 and .92, and the test-retest reliability (2-8 weeks) is .51-.67.

##### Cognitive Emotion Regulation Questionnaire

The Cognitive Emotion Regulation Questionnaire covers 9 strategies (self-blame, blaming others, acceptance, refocusing on planning, positive refocusing, rumination or focus on thought, positive reappraisal, putting into perspective, and catastrophizing) and 36 items of cognitive emotion regulation with a range from 1 ([almost] never) to 5 ([almost] always) [71]. The German version differs in the item number. Here the questionnaire was shortened to 27 items (3 items per dimension) [72,73]. A good psychometric quality (factorial validity and acceptable-to-good reliability [.70<α<.84]) could be shown in a clinical sample [72].

##### Emotion Regulation Questionnaire

The Emotion Regulation Questionnaire deals with the most common preferences of 2 applied strategies for emotion regulation: suppression (4 items) and reappraisal (6 items) [74]. The German version was first published in 2009 [75]. On a 7-point Likert scale from 1 to 7 (1=not correct at all; 4=neutral; and 7=completely correct), the participants can choose a number. Internal consistency (Cronbach α) for reappraisal was .79, and for suppression, .73 [74]. The test-retest reliability across 3 months was .69 for both strategies [74].

##### Anxiety Sensitivity Index-3

Anxiety Sensitivity Index-3 is an 18-item scale with 3 factors (physical, cognitive, and social concerns) on a 5-point Likert scale [76]. The German version was first published in 2009. The internal consistency is between .86 and .89 [77]. Satisfactory measurement accuracy and good validity can be seen in comparison with the English version [77].

##### Self-compassion Scale (German Version)

The Self-compassion Scale (SCS) contains 26 items with originally 3 basic components: (1) self-kindness, (2) common humanity, and (3) mindfulness, which are answered on a 5-level scale (1=very rarely and 5=very often) [78]. The German version of the SCS (SCS-D) was first checked for reliability and validity in 2011 [79]. In comparison with the original, a 6-factorial structure (self-kindness, self-condemnation, common humanity, isolation, overidentification, and mindfulness) was found and as expected, correlates with subjective well-being and psychological strain. With the German version of the SCS, an economic, reliable, and valid assessment of self-compassion is available.

##### Perceived Stress Scale-10

The Perceived Stress Scale (PSS-14) contains 14 items, which are answered on a 5-point response scale (0=never and 4=very often) [80]. On the basis of principal component analysis, a low factor loading of 4 items was determined and then dropped. The shortened PSS-10 shows a slightly increased reliability (Cronbach α=.78 vs Cronbach α=.75) and a similar validity [81]. The German version of the PSS-10 shows good internal consistency (Cronbach α=.84) and construct validity between perceived stress and depression, anxiety, fatigue, procrastination, and quality of life [82,83]. PSS-10 is an economic, reliable, and valid assessment tool for assessing perceived stress.

##### Trier Inventory for the Assessment of Chronic Stress–Screening Scale for Chronic Stress

The TICS-SSCS (Trier Inventory for the assessment of Chronic Stress–Screening Scale for Chronic Stress) comprises 12 items [84]. The TICS-SSCS measures the frequency of self-perceived overall stress in 5 different stress domains in the past 3 months: chronic worrying, work-related overload, social overload, excessive demands, and lack of social recognition. The frequency of stress in the 5 stress domains is recorded with the values *never* (0 points), *rarely* (1 point), *sometimes* (2 points), *frequently* (3 points), and *very frequently* (4 points), and in the end, an average score can be calculated. The internal consistency for the TICS-SSCS is rated as very good, with Cronbach α=.91 [84,85].

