### Objectives

In this study, we implement an 8-week randomized controlled trial of a web-based, individualized physical exercise training intervention to evaluate the link between aerobic capacity and resilience in healthy untrained adults. Therefore, baseline values of performance diagnostics to determine the innate aerobic capacity (VO_2_peak) as well as emotion regulation abilities, stress reactivity, and stress recovery (saliva cortisol) as potential resilience mechanisms are estimated. We hypothesize that (1) participants with a high innate aerobic capacity will show a higher resilience to stress compared with participants with low aerobic capacity. This will be followed by 8 weeks of individualized web-based physical exercise training combining continuous and interval-type running exercises with the aim of progressively increasing aerobic capacity. After completion of the exercise intervention, performance diagnostics will be repeated to estimate the acquired aerobic capacity, as well as to assess the psychological parameter. In addition, secondary outcomes of molecular factors, including hair cortisol levels, endocannabinoids, catecholamines, cytokines, and cell-free DNA, and results of several questionnaires will be determined throughout the study. We hypothesize that (2) the exercise intervention will improve the aerobic capacity of the intervention group, which (3) will be accompanied by improvements in resilience factors. This will offer the possibility to exploratively study the underlying molecular mechanism (stress hormone release and immune reactions) in the promotion of resilience by regular physical activity.

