## Methods

### Trial Design and Participants

This study is designed as a prospective randomized controlled trial with 2 phases of data collection before (baseline examination; time point 0 [T0] and time point 1 [T1]) and after (final examination; time point 2 [T2] and time point 3 [T3]) 8 weeks of web-supervised physical exercise training intervention (T1-T2; Figure 1). The multidisciplinary single-center trial is a collaboration among the Institute of Physiological Chemistry, Department of Psychiatry and Psychotherapy, Department of Clinical Psychology and Neuropsychology, and Department of Sports Medicine, Disease Prevention and Rehabilitation. The medical association Rhineland-Palatinate approved the study (July 29, 2019, ID: 2019-14305), and the study was registered with the German Clinical Trials Register (DRKS; DRKS00018078; October 2, 2019) and conformed to the standards of the Declaration of Helsinki of the World Medical Association. Administrative changes of the protocol, if needed, are minor corrections and clarifications that have no effect on the way the study is to be conducted. An amendment will be approved by the Ethics Committee Landesärztekammer Rhineland-Palatinate before implementation. This protocol follows the guidelines from the SPIRIT (Standard Protocol Items: Recommendations for Interventional Trials) [53] and the CONSORT-eHEALTH checklist (Multimedia Appendix 1) [54]. A SPIRIT diagram of enrollment, interventions, and assessments is provided in Figure 1.

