**Figure 1 figure1:**
[figure not shown]
SPIRIT (Standard Protocol Items: Recommendations for Interventional Trials) diagram of enrollment, interventions, and assessments. ADS: Allgemeine Depressionsskala; ASI: Anxiety Sensitivity Index; BRS: Brief Resilience Scale; BSI: Brief Symptom Index; CERQ: Cognitive Emotion Regulation Questionnaire; CG: Control Group; CTQ: Childhood Trauma Questionnaire; ECG: electrocardiogram; ERQ: Emotion Regulation Questionnaire; GOT: Glutamate Oxalacetate Transaminase; GPT: Glutamate Pyruvate Transaminase; GSE: General Self-Efficacy Scale; HPA: Habitual Physical Activity Questionnaire; IG: Intervention Group; IPAQ: International Physical Activity Questionnaire; MDBF: Mehrdimensionaler Befindlichkeitsfragebogen; PAR-Q: Physical Activity Readiness Questionnaire; PSS-10: Perceived Stress Scale–10; SCS-D: Self-compassion Scale–German Version; SECPT: socially evaluated cold pressor test; SF-36: Short-Form Health Survey; SRS: Stress Reactivity Scale; TICS-SSCS: Trier Inventory for the assessment of Chronic Stress–Screening Scale For Chronic Stress.

The primary (VO_2_peak and saliva cortisol) and key secondary outcomes, trial methods, and designs are summarized in the World Health Organization trial registration data set (Textbox 1). This study includes 4 time points of investigation of physiological and psychological parameters, including the primary end points of a change in VO_2_peak and saliva cortisol from the baseline: at T0 and T1, baseline values will be estimated, and at T2 and T3, data collection following the control or exercise intervention will be performed. T0 and T2, as well as T1 and T3, are structured in the same way, except for the separately listed psychological examinations at the measurement points. T1 and T3 will be performed after a maximum of 10 days after T0 and T2, respectively. Written consent after a detailed oral explanation will be obtained from all participants at the beginning and after completion of the study by the responsible study physician. At the beginning of the study (T0), the participants will not be fully informed about the purpose and aim of the psychological stress tests. Full clarification will take place at T3. If a participant wishes to discontinue the study prematurely, they will be fully informed about the purpose and aim of the psychological stress tests.

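### The hair-length exclusion does not secure the 2 cm strand needed for the 2-month cortisol value; a lesser point is that the 3-month TICS-SSCS recall at T2 reaches 4 to 5 weeks before training

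*Protocol article*

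**What the plan says.** **Hair cortisol.** The Preliminary Investigation section states: "To determine the long-term cortisol value over 2 months, a 2 cm–long strand of hair will be cut off". The strand is taken directly at the skin at T0, and the measurement is repeated after the intervention at T2 or T3. The exclusion criteria in Textbox 2, and the key exclusion criteria in the trial registration data set, rule out only participants with hair shorter than 1 cm. The Objectives list "secondary outcomes of molecular factors, including hair cortisol levels, endocannabinoids, catecholamines, cytokines, and cell-free DNA, and results of several questionnaires", so hair cortisol is a named secondary outcome. Statistical Methods says that missing data will be left out of the data set.

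**TICS-SSCS.** Its own section states: "The TICS-SSCS measures the frequency of self-perceived overall stress in 5 different stress domains in the past 3 months". The questionnaire section is headed for T0 and T2. Only the Brief Resilience Scale and the Childhood Trauma Screener are marked as T0 only, so the TICS-SSCS is repeated at T2. Training lasts 8 weeks, between T1 and T2 (Trial Design and Participants). The same section adds: "T1 and T3 will be performed after a maximum of 10 days after T0 and T2, respectively". No shorter recall period is stated for T2.

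**The concern.** The hair criterion evidently exists to make the hair assay possible, but its threshold is half the length that the assay description requires. Someone who just meets it cannot supply the specified strand. Either the value is missing, or a shorter strand is used and the value covers a shorter period. If hair length also changes between visits through growth or a haircut, the baseline and post values of one person describe periods of different length, and their difference is no longer a clean before/after comparison.

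The TICS-SSCS question is separate and smaller. At T2 its recall period is longer than the training period, so part of the post-intervention answer describes weeks before training began. Some of those weeks were already rated at T0. A real fall in chronic stress could therefore appear smaller than it was.

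**Working it through.** The document gives no calculated figure for these windows, apart from equating 2 cm of hair with 2 months. What follows is calendar arithmetic on its stated lengths.

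**Inputs:** 2 cm strand for 2 months (Preliminary Investigation); exclusion below 1 cm (Textbox 2, registration data set); 3-month recall (TICS-SSCS section); 8 weeks of training from T1 to T2, and at most 10 days from T0 to T1 and from T2 to T3 (Trial Design and Participants). One month = 365.25 / 12 / 7 = 4.35 weeks, with a 4-week month as the alternative reading.

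**Hair**
- Implied growth: 2 cm / 2 months = 1 cm per month.
- A full 2 cm strand covers 2 × 4.35 = 8.70 weeks. Taken at T2, directly after week 8, it starts 8.70 − 8 = 0.70 weeks before training. Taken at T3, 10 days (1.43 weeks) later, it starts 8 + 1.43 − 8.70 = 0.73 weeks after training began. The planned window therefore fits the 8 weeks well.
- At the admitted minimum, 1 cm covers 4.35 weeks, which is half of the stated 2 months and 4.35 / 8 = 54% of the training period. Lengths of 1.0 to 1.9 cm give about 1.0 to 1.9 months.
- Example of a change within a person: from T0 to T2 is 8 to 8 + 1.43 = 9.43 weeks. At the implied rate, uncut hair grows 8 / 4.35 = 1.84 cm to 9.43 / 4.35 = 2.17 cm. Someone with 1 cm at T0 could then give a full 2 cm at T2, so a 1-month baseline value would be set against a 2-month post value. A haircut between visits does the reverse.

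**TICS-SSCS**
- Recall: 3 × 4.35 = 13.04 weeks (12 with 4-week months).
- Part before training, if T2 directly follows week 8: 13.04 − 8 = 5.04 weeks, and 5.04 / 13.04 = 39%. With 4-week months: 12 − 8 = 4 weeks, and 4 / 12 = 33%.
- If T2 came 10 days late (an assumption; the document sets no such delay): 13.04 − 8 − 1.43 = 3.6 weeks.
- Overlap of the T2 and T0 recall windows: 13.04 − 8 − gap from T0 to T1, which is 5.0 weeks for no gap and 3.6 weeks for a 10-day gap (4.0 and 2.6 weeks with 4-week months).
- If, and only if, the score behaves as a simple time average of stress, a constant effect during training would show at 8 / 13.04 = 61% of its size (8 / 12 = 67% with 4-week months).

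**The case against.** The strongest reply is that the stakes are small. Neither measure is primary: the primary outcomes are VO2peak and salivary cortisol, and the TICS-SSCS is one of many scales, not singled out as an endpoint. The recall overlap is the same in both randomized arms. Randomization is stratified by gender, so any loss of hair samples that follows gender should be roughly balanced. All of this stands, and it limits the consequence to attenuation and missing or uneven data in secondary outcomes.

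A reader might infer that neither look-back window fits the 8-week intervention. The documents do not support that for hair: the 2 cm window fits closely, and the fault lies in the eligibility threshold alone.

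A reader might also take the 61% as the expected shrinkage of a TICS-SSCS effect. The scale asks for frequency ratings and nothing is said about how respondents weight time, so the figure is only an illustration under an assumption. Nor do the documents state a separate objective of showing that training lowers long-term stress. The hypotheses concern aerobic capacity and resilience.

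It may be said, too, that nothing allows strands under 2 cm, so short hair would simply mean a missing value. That is possible, but it leaves the criterion admitting people who cannot contribute to a named outcome. That such people are mostly men is plausible, but no figure supports it.

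Finally, the questionnaires are repeated 12 weeks after T3. A 13.04-week recall then starts about 1 week before T3, so it falls almost wholly after training. That makes the 3-month form reasonable for the follow-up, but it does not alter what the T2 score covers.

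**Conclusion.** The hair point holds as a conflict between two stated figures. The exclusion secures 1 cm, the sample needs 2 cm, and people between the two can give at best about 1.0 to 1.9 months instead of 2. The comparison of baseline with post can then be missing or rest on unequal windows within a person. How many are affected cannot be judged from the document, and the month conversion rests on its own 1 cm per month.

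The TICS-SSCS point holds as a minor limit on interpretation. About 4 to 5 weeks of the T2 window (33% to 39%) precede training, assuming that T2 directly follows week 8. The risk is a missed effect on one secondary scale; the comparison between arms is not biased. Neither point touches the primary outcomes.

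**What to change.** **Hair.** Choose one rule and state it.
- For each person, analyse the same proximal segment length at both visits (the shorter of the two available) and report that length. This also deals with haircuts between visits, and it can be applied to the 31 completers if their strands or strand lengths were kept (an assumption). The cost is a shorter window for some: a 1 cm segment at T2 covers only about the last 4.35 of the 8 weeks.
- Or raise the exclusion to hair under 2 cm for the remaining recruits, in both Textbox 2 and the registration data set. Recruitment is paused at 43 of 70, so up to 70 − 43 = 27 entries could follow the new rule. The cost is an amendment and a few short-haired volunteers, and it does not by itself prevent a haircut before T2 or T3.

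**TICS-SSCS.** Keep the validated 3-month wording at both visits. State that the T2 window is partly before training and overlaps the T0 window, and that a null T2 change will not be read as evidence that training has no effect on chronic stress. This costs one sentence. Do not reword T2 alone to 8 weeks: that would set a 3-month score against an 8-week score on an altered scale. Do not substitute the PSS-10 unless its recall period is confirmed, because the document does not give one.
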